### SA group

The positioning of non-acupoints adheres to the following two principles: first, the sites of non-acupoints are selected away from the meridians or conventional acupoints; second, the distribution areas of non-acupoints are similar to that of the acupuncture acupoints to avoid patients differentiating groups by the location of acupoints. Five non-acupoints will be selected for the treatment of the SA group (Table 2). Unlike the TA group, the SA group will not perform manual operations for needles after needle insertion and pretend to perform the manual operation of *deqi* every 10 minutes during needle retention time.

**Table 2 Tab2:** Locations of non-acupoints for the SA group

Non-acupoint	Location
Non-acupoint 1	On the abdomen, 2 cun^a^ superior to anterior superior iliac spine, between the gallbladder meridian and the spleen meridian
Non-acupoint 2	On the abdomen, 2 cun inferior to the navel, 1 cun beside the anterior midline, between the kidney meridian and the stomach meridian
Non-acupoint 3	On the lateral aspect of the leg, 3 cun inferior to GB34, between gallbladder meridian and bladder meridian
Non-acupoint 4	On the leg, 2 cun superior to the medial malleolus, in the middle of the medial tibia, between the liver meridian and the spleen meridian
Non-acupoint 5	On the leg, the midpoint of the line between GB40 and ST41, between the gallbladder meridian and the stomach meridian

^a^1 cun (≈ 20 mm) is defined as the width of the interphalangeal joint of the participant’s thumb

All participants will be advised to keep their routine diets and lifestyles during the study procedure. Loperamide (Imodium, Xian Janssen Pharmaceutical Ltd., China), will be used as a rescue medication under the guidance of gastroenterologists whenever necessary. The medication status and other non-irritable bowel syndrome drug applications of participants will be strictly recorded during the trial.

### Sample size

The sample size calculation was based on the composite response rate of the primary endpoint in our pilot study (not yet published). The results of our pilot study showed that a sham acupuncture response rate of 27% and a true acupuncture of approximately 45% were estimated for the primary endpoint. A sample size of 222 evaluable participants was calculated to be needed for 80% power. With an estimated dropout rate of 20% and the balance of recruitment quotas in 5 sites, 280 randomly allocated participants were planned.

### Randomization, sequence generation, and blinding

Eligible participants will be randomly assigned to the TA group and SA group according to the ratio of 1:1 by central stratified block randomization in the REDCap EDC system with a dynamic block size. The randomization sequence was created by a biostatistician who did not participate in this trial. Recruiters will be responsible for registering the participants, and acupuncturists will assign the participants to the intervention. The different REDCap EDC system permissions depend on the role of the personnel. Only the acupuncturist and his or her assistant can obtain the randomization grouping information. The clinical recruiters, outcome assessors, data managers, and statisticians will be blinded to the group allocation.

### Outcomes and follow-up

The primary endpoint is a composite response rate at week 6 in accordance with the FDA recommendations. A participant is defined as a composite responder when he or she is a responder in both abdominal pain intensity and stool consistency. The definition of abdominal pain intensity responder is defined as a decrease in the weekly average of worst abdominal pain in the past 24 h score of at least 30% compared with baseline. Stool consistency responder is defined as a decrease of at least 50% in the number of days per week with at least one stool that has a consistency of type 6 or 7 compared with baseline.

The secondary endpoints also include composite response rates at other weeks (weeks 2, 4, 10, 14, and 18). The IBS Symptom Severity Scale (IBS-SSS) is used to evaluate the overall symptoms of IBS, which comprises 5 domains (severity of abdominal pain, frequency of abdominal pain, severity of abdominal distension, degree of dissatisfaction with defecation habits, and interference with the quality of life) that are scored from 0 to 100, and total score range 0 to 500. A decrease of 50 points is considered as a minimal clinically important difference [20]. The IBS Quality of Life (IBS-QoL) comprises 34 IBS-specific items which divide into 8 variables: health worries, food avoidance, body image, dysphoria, interference with activity, social reactions, sexual activity, and relationships [21]. The IBS-QoL score will be transformed into a 0–100 scale using the following formula: (the actual raw score − the lowest possible score)/possible score range × 100. The Patient Health Questionnaire-9 (PHQ-9) is a diagnostic instrument for common mental disorders, of which scores range from 0 to 27 and the mental state is inversely proportional to the total score of it [22]. Individual IBS symptoms (abdominal pain, abdominal bloating, stool frequency) will also be collected and analyzed. The Adequate Relief (AR) scale will be used to confirm whether participants have an adequate relief by a two-category (yes or no) answer. IBS-SSS, IBS-QoL, PHQ-9, AR scale, and individual symptoms will be evaluated at weeks 2, 4, 6, 10, 14, and 18.

For blinding assessment, all participants will be asked to guess which treatment they received at the end of the last treatment in week 6. Additionally, the Credibility/Expectancy Questionnaire within 5 min will be used to evaluate the credibility and expectancy of participants after the first treatment [23]. The schedule of enrollment, intervention, and assessments is shown in Fig. 2. The incidence of AEs and any use of loperamide will be recorded at 6-week treatment and 12-week follow-up.

**Fig. 2 Fig2:**
[figure not shown]
Schedule of enrollment, intervention, and assessments

### Human body data retention

Considering that the different types of testing instruments in different hospitals will affect the results of sample analysis, we will carry out the sample retention work from Dongfang Hospital Beijing University of Traditional Chinese Medicine. Stool samples and functional magnetic resonance imaging (fMRI) data at baseline and at the end of the intervention will be collected with the participants’ consent. It is well established that in IBS, communication between the gut and the brain is impaired, resulting in bowel movement disorders, visceral hypersensitivity, and altered central nervous system processing [24]. Through neuroimaging technology, the cooperative regulation mechanism of the “gut-brain” axis can be explored, which provides an important theoretical support for the study of the acupuncture effect. Based on the literatures, we will focus on the pain inhibition and conduction pathway and the emotion regulation pathway [25]. The MRI details were acquired via a 3.0-T Siemens scanner (Skyra, Siemens, Erlangen, Germany), and the data can be divided into two main categories including rest-state fMRI (rs-fMRI) and diffusion tensor imaging (DTI). Additionally, a gut microbiota analysis will be performed to assess the species abundance spectra or microbiota diversity. Bacterial DNA will be investigated by 16S rRNA gene sequencing targeting the hypervariable V3–V4 regions [26].

### Data management and monitoring

All researchers will be required to strictly protect the individual privacy of the participants. The electronic case report form (eCRF) will be used to input the general information and evaluation content related to the trial. Dynamic management will be performed to ensure complete, timely, and accurate data collection using the verification function in eCRF, and the researchers will no longer be able to modify the content of eCRF, because the database will be locked by the data management team when the trial is completed. In order to facilitate the elderly or other participants who are inconvenient to use electronic devices, we will also provide corresponding paper materials (e.g., defecation diary cards). Both paper files and electronic documents will be preserved for at least 5 years after publication. If readers and reviewers have any questions, they can contact the corresponding author for access to the original data.

Experts in acupuncture, gastroenterology, methodology, and statistics will review and revise the protocol. Before the trial, all researchers will be trained on standard operating procedures (such as screening patients, acupuncture, filling in eCRF, evaluation results, and data management). Online monitoring and on-site monitoring will be adopted in this trial. All modifications of the data can be traced through the eCRF. Appropriate communication will be maintained with the patients to strengthen their compliance and ensure data integrity. In addition, a Data Safety and Monitoring Board (DSMB) will be independently established to review and interpret the data of the trial. The board will review the progress of the trial, independently of the investigators, and decide whether the trial needs to be terminated early solely on the basis of adverse events.

### Statistical analyses

The following hypothesis will be tested simultaneously for the primary outcome:H0: There is no difference in the response rate between the TA and SA groups.H1: There is a significant difference in the response rate between the TA and SA groups.

All analyses related to the treatment efficacy will be based on the intention-to-treat (ITT) population, defined as all randomly assigned participants with baseline data. Safety analyses will be based on the safety population who have received at least one treatment after randomization and have safety indicator records. Missing data will be imputed using multiple imputation.

Continuous data will be represented by mean ± standard deviation (M±SD) or median combined with interquartile range, while categorical data will be represented by frequency, constituent ratio, and percentage. For the primary endpoint, the chi-square test will be used for the comparison of the two groups. For the secondary endpoints, Student’s *t* test or Wilcoxon rank-sum test will be used to assess the continuous variables between group comparisons, and the chi-square test or Fisher exact tests will be used to evaluate the categorical variables between the groups. The safety population will be used to analyze the incidence of AEs between the groups. The *P* value less than 0.05 will be considered as statistically significant. All analyses will be performed using SAS 9.3.

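### The primary chi-square ignores the randomisation strata and the baseline severity already collected; a stratified or adjusted analysis could add about 0 to 6 points of power at almost no cost

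*Protocol article*

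**What the plan says.** **Primary test.** Statistical analyses states the null hypothesis as "H0: There is no difference in the response rate between the TA and SA groups" and the test as "For the primary endpoint, the chi-square test will be used for the comparison of the two groups". A P "value less than 0.05 will be considered as statistically significant". No stratification factor or covariate is named for this comparison.

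**Allocation.** Randomization, sequence generation, and blinding says participants are assigned "according to the ratio of 1:1 by central stratified block randomization in the REDCap EDC system with a dynamic block size". It does not say what the strata are. Trial design lists 6 hospitals, while Sample size refers to recruitment quotas in 5 sites. Neither section says that site is the stratum.

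**Baseline data.** The inclusion criteria set thresholds for average daily pain and for days with stool type 6 or 7. Outcomes and follow-up defines response as a fall of at least 30% in weekly average worst pain and of at least 50% in type 6/7 days per week, both against baseline. Both baseline measures are therefore needed to score the primary endpoint.

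**Missing data.** "Missing data will be imputed using multiple imputation".

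**Sample size.** The planning rates are taken from the pilot: 27% response on sham and about 45% on true acupuncture. For the size itself the article says: "A sample size of 222 evaluable participants was calculated to be needed for 80% power". Allowing for 20% dropout and for site quotas, it then plans to randomise 280.

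**The concern.** Stratified blocks force the arms to be balanced within strata. If response differs between strata, that balance removes the between-stratum part of the variation from the treatment comparison. The plain chi-square standard error still counts it, so the test becomes conservative and the precision that the stratification bought goes unused. The same applies, usually more strongly, to a baseline measure that predicts response: adjusting for it sharpens the comparison, and a 2×2 table cannot.

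This is a method the article states, not a detail left for later. The design gives some reason to expect strata to matter if they are sites: each sub-center has only 1–2 acupuncturists, who treat both arms, so site and operator largely coincide. The Background also reports that the pilot's response rates did not differ significantly and points to its sample size. Power that needs no additional participants is therefore worth having.

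**Working it through.** **1. Reproduce the planned size.** Inputs from Sample size and Statistical analyses: p₀ = 0.27, p₁ = 0.45, power 80%, alpha 0.05, 1:1 allocation. Two-sided testing is implied by the hypotheses but not stated.

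n per arm = [z₀.₉₇₅·√(2p̄(1−p̄)) + z₀.₈₀·√(p₀(1−p₀) + p₁(1−p₁))]² / (p₁−p₀)², with p̄ = 0.36

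= [1.960·√0.4608 + 0.842·√0.4446]² / 0.18² ≈ (1.330 + 0.561)² / 0.0324 ≈ 110.4, so 111 per arm and 222 in total.

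This matches the article exactly and is the formula for an uncorrected chi-square. Power at 111 per arm is 80.2%. For dropout, 222/0.80 = 277.5, so 278; the stated 280 equals 5 × 56. The named test and the sample size agree with each other.

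**2. What adjustment could add.** Simulation with N = 222, 6 equal sites (37 each) as the assumed strata, allocation balanced within site, and complete data. Marginal rates were 27% v 45% for power and 27% v 27% for type I error, with 3,000 runs per scenario. Assumed, because the article gives neither: a site SD on the logit scale, and the effect of one standardised baseline covariate (log-odds per SD). The adjusted test is the Wald test of arm in a logistic model with site and that covariate.

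| Site SD / baseline effect | Power: chi-square | Power: CMH by site | Power: adjusted logistic | Type I error: chi-square / CMH / logistic |
|---|---|---|---|---|
| 0 / 0 | 80.7% | 80.5% | 81.0% | 5.5 / 5.3 / 5.4% |
| 0.3 / 0.3 | 80.8% | 81.2% | 82.9% | 4.8 / 4.8 / 4.8% |
| 0.5 / 0.5 | 80.5% | 81.9% | 84.3% | 5.0 / 5.2 / 5.2% |
| 0.8 / 0.5 | 82.5% | 84.7% | 86.8% | 4.2 / 5.1 / 5.4% |
| 0.5 / 0.8 | 80.8% | 81.4% | 85.3% | 4.5 / 4.7 / 4.7% |
| 0.8 / 0.8 | 80.8% | 82.7% | 86.9% | 4.3 / 5.1 / 5.1% |

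Gain over the chi-square, from the rounded figures:
- CMH: −0.2 to 2.2 points, that is, about 0 to 2.
- Adjusted logistic: 0.3 to 6.1 points, that is, about 0 to 6.

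The Monte Carlo standard error is about 0.7 points for power (√(0.8·0.2/3000)) and 0.4 points for type I error. The three tests were run on the same simulated data sets, so their differences are firmer than the separate figures.

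**3. Repeat.** A second simulation at N = 222 gave chi-square v adjusted logistic power of 79% v 79% at 0/0, 82% v 85% at 0.5/0.5 and 83% v 88% at 0.8/0.8. Chi-square type I error was about 4.4 to 5.3%.

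**4. With imputation.** 276 randomised, 6 equal sites, 20% missing completely at random, 20 imputations, 700 runs per scenario. A pooled chi-square (D2 method) v adjusted logistic pooled by Rubin's rules had power of 79% v 81% at 0/0, 82% v 86% at 0.5/0.5 and 80% v 86% at 0.8/0.8. Type I error was 4 to 6% throughout. The gain is of the same order as with complete data.

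**5. Reading the assumed range.** For a central site with 27% response, logit(0.27) = −0.995. One SD either side spans about 18% to 38% at SD 0.5 and about 14% to 45% at SD 0.8. The upper end is a wide spread between hospitals.

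**The case against.** The case for leaving the plan alone is a fair one. The chi-square is valid, it is the test the sample size was built for, and it delivers the stated 80%. The gain depends on effects that the article does not document. Response is a percentage change from each participant's own baseline, so baseline is already partly in the endpoint and may predict little more. Staff are uniformly trained, which argues against large site differences.

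All of that stands, and it limits the size of the point. It does not remove it: when neither stratum nor baseline matters, adjustment loses nothing visible in the simulations, and when either does, it gains.

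A reader might also infer stronger things that the article does not support:
- **That randomisation is stratified by site.** The factor is not named. Site fits a multi-center design with site quotas, but it remains an inference.
- **That the trial is underpowered or the test invalid.** Step 1 shows that the planned power is met, and the chi-square type I error stays near or below 5%.
- **That the loss is larger, or the chi-square markedly conservative.** This needs a site SD of about 1.0 on the logit scale, and nothing in the article supports such a spread.
- **That a chi-square cannot be used with multiple imputation.** It can. The difference in proportions and its standard error pool by Rubin's rules, and methods for pooling chi-square statistics exist (step 4 uses one). The unstated pooling rule is a detail that an article may leave to the SAP.

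**Conclusion.** The point holds as an efficiency improvement to a stated method, not as an error. The primary test leaves out the strata that the design balances on and two baseline measures that are collected anyway. The power forgone is about 0 to 2 points from the strata alone and about 0 to 6 points in total if baseline severity is also prognostic. It is nil if neither predicts response.

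These figures assume site as the stratum with 6 equal sites, a site SD and a baseline effect each between 0 and 0.8 on the logit scale, and a single covariate standing in for the two baseline measures. The direction is secure; the size within that range is not known from the article.

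**What to change.** Before unblinding:

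1. Name the randomisation stratum or strata. If site is one, reconcile the 5 sites in Sample size with the 6 hospitals in Trial design.
2. Make the primary analysis a logistic regression of week-6 composite response on arm, the actual strata, baseline weekly worst-pain score and baseline type 6/7 days per week.
3. Report a standardised risk difference with 95% CI, pooled over imputations by Rubin's rules. This keeps the result on the response-rate scale of the hypotheses and the sample size, which a conditional odds ratio would not.
4. If a model is not wanted, use a CMH analysis stratified by the actual strata as the minimum.
5. Keep the chi-square as a supportive analysis.

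No new data or participants are needed, and 222/280 can stay. The cost is a change to the primary analysis while the trial is recruiting. It has to be recorded as a change to the analysis plan in the registry, as the article's Protocol section already provides.

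### The continuous secondary endpoints are compared with no baseline covariate: valid tests, but less precise than the data allow

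*Protocol article*

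**What the plan says.** The Statistical analyses section gives Student's t test as one option for continuous secondary endpoints and continues with the other: "Wilcoxon rank-sum test will be used to assess the continuous variables between group comparisons". Neither that section nor the rest of the article mentions a covariate, an analysis of covariance or a longitudinal model.

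The Outcomes and follow-up section sets six post-baseline assessments: "IBS-SSS, IBS-QoL, PHQ-9, AR scale, and individual symptoms will be evaluated at weeks 2, 4, 6, 10, 14, and 18". The Adequate Relief scale is a yes/no answer and falls outside this point.

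Baseline information is part of the design. The intention-to-treat population is "defined as all randomly assigned participants with baseline data", and the pain responder definition requires a fall in "score of at least 30% compared with baseline". Missing data are to be handled by multiple imputation, with no imputation model described. Randomization is stratified, but the factors are not named.

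**The concern.** A person's baseline score usually predicts that person's later score. A two-sample test on follow-up scores leaves that predictable variation in the error term. A test on change scores removes it by subtraction, which over-corrects whenever the regression slope of follow-up on baseline is below 1. Analysis of covariance estimates the slope instead and, apart from a negligible loss of degrees of freedom, is never less precise than either.

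The stake is the width of the confidence intervals for the secondary outcomes, and hence the chance of detecting a real effect on them. The Background section gives insufficient sample size as a reason why the pilot was inconclusive, so unused information matters in this programme. The article states its choice of test, so this is not a detail merely left to a later document.

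**Working it through.** **Plan's own figure.** The article assumes response rates of 27% and 45% with 80% power. The significance level is 0.05 ("value less than 0.05 will be considered as statistically significant"), taken as two-sided because the alternative hypothesis is non-directional: "There is a significant difference in the response rate between the TA and SA groups". With the pooled-variance formula and a mean rate of 0.36:

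n per arm = [1.960 × √(2 × 0.36 × 0.64) + 0.842 × √(0.27 × 0.73 + 0.45 × 0.55)]² / 0.18² = 110.4, so 111 per arm and 222 in total.

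Allowing for 20% dropout, 222 / 0.8 = 277.5, or 278, which is consistent with 280. The figure reproduces. It concerns only the binary primary endpoint, so nothing below changes it.

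**Inputs for the continuous endpoints.** There are 111 evaluable per arm (from the Sample size section). The correlation r between baseline and follow-up is assumed to be 0.3, 0.5 or 0.7, as the article gives neither a correlation nor an SD. Differences are therefore expressed in units of the follow-up SD, σ. The change-score formula also assumes the same SD at baseline and follow-up.

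**Variance of the between-arm difference, n per arm.**
- t test on follow-up scores: 2σ²/n
- t test on change scores: (2σ²/n) × 2(1 − r)
- baseline-adjusted (ANCOVA): (2σ²/n) × (1 − r²)

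The ratio of adjusted to follow-up-score variance is 1 − r². The ratio of adjusted to change-score variance is (1 − r²) / [2(1 − r)] = (1 + r)/2.

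| | r = 0.3 | r = 0.5 | r = 0.7 |
|---|---|---|---|
| Adjusted / follow-up-score variance | 0.91 | 0.75 | 0.51 |
| Variance saved | 9% | 25% | 49% |
| Equivalent sample-size factor | 1.10 | 1.33 | 1.96 |
| Adjusted / change-score variance | 0.65 | 0.75 | 0.85 |
| Variance saved | 35% | 25% | 15% |
| Equivalent sample-size factor | 1.54 | 1.33 | 1.18 |

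**In terms of detectable difference.** The follow-up-score t test has 80% power at (1.960 + 0.842) × √(2/111) = 0.376 SD. Multiplying by √(1 − r²) gives 0.359, 0.326 and 0.269 SD with adjustment. Multiplying by √[2(1 − r)] gives 0.445, 0.376 and 0.291 SD for a change-score test.

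**In terms of power at a true difference of 0.376 SD.**

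| Analysis | r = 0.3 | r = 0.5 | r = 0.7 |
|---|---|---|---|
| Follow-up score | 80% | 80% | 80% |
| Change score | 65.8% | 80% | 95.1% |
| Baseline-adjusted | 83.6% | 89.9% | 97.5% |

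At r = 0.5 the baseline score does the work of 111 / 0.75 = 148 participants per arm instead of 111.

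**The case against.** The best defence is that nothing here is invalid. Two-sample tests keep their type I error under randomization, and chance baseline imbalance is covered by the interval and is not bias. No passage is contradicted and no stated figure is wrong. All of that stands, and it limits the point to efficiency.

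Second, the article may intend change scores. The IBS-SSS reference value is worded as a fall ("A decrease of 50 points is considered as a minimal clinically important difference"), which is compatible with that. The text does not settle it, so both readings are shown. The choice reverses the order of the savings across r, and quoting only the largest figure, 1.96 times the sample size, would overstate the case. Adjustment is still more precise on either reading.

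Third, r is assumed throughout, and the variance factors are exact for the t test, not for the rank-sum test. The size is therefore a range.

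Fourth, the schedule figure is not available, so baseline measurement of each scale is implied, not shown.

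A reader might also infer two stronger faults. One is that repeated visits do nothing for missing data. The article plans multiple imputation, which can draw on baseline and on other visits, so the text does not support this. The other is that choosing between t and rank-sum lets the estimand drift from visit to visit. The article gives no selection rule, and such a rule is commonly left to the full protocol or analysis plan, so its absence proves nothing. That the tests would be run separately at each week is likewise a natural inference, not a statement in the text.

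**Conclusion.** The point holds as one of efficiency. The named tests carry no baseline covariate, and adjustment would reduce the variance of the treatment difference whether follow-up or change scores are meant. For r between 0.3 and 0.7, the 95% confidence intervals would be 5% to 29% narrower than with follow-up scores, or 19% to 8% narrower than with change scores.

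These sizes rest on the assumed r, on equal SDs at the two times for the change-score comparison, and on each scale having a baseline value. The primary analysis and the sample size stand as they are. The documents do not support reading this as bias, as mishandled missing data or as a shifting estimand. The change is worth making because it costs so little, not because the secondary results would otherwise be wrong.

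**What to change.** In the Statistical analyses section, replace the t and rank-sum tests for IBS-SSS, IBS-QoL, PHQ-9 and the continuous individual symptoms with one pre-specified baseline-adjusted analysis:

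- either ANCOVA at each week, with arm, baseline score and the randomization strata;
- or one mixed model for repeated measures per endpoint, with baseline score, arm, week, arm-by-week and the randomization strata.

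Report the week-6 adjusted mean difference with 95% CI as the main contrast and the other weeks as supportive.

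State how the model and the multiple imputation fit together. With ANCOVA, for example, the model can be fitted in each imputed data set and the estimates pooled. With the mixed model, say whether it is fitted to observed or imputed data. Confirm that each scale is measured at baseline.

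The composite response at other weeks needs no change here. Keeping the chi-square test there matches the week-6 primary analysis.

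The cost is a few sentences and standard code in the SAS software already named. If the baseline scores are collected as implied, no new data or visits are needed. The trial is recruiting, the statisticians are blinded, and the Protocol section provides for registering changes to the analysis plan, so the change can be made before unblinding.
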